### Quality control

2.15

To ensure the control group's compliance, participants will receive the Climen tablets of a week dose at the face-to-face interview every week, and sign on the medicine record of the CRF. In addition, researchers will communicate with them every day to visit their medication via call, WeChat, short message, etc.

All of the acupuncturists who take part in this trial have gained medical licenses in China and have been well trained according to the trial's procedure under the guidance of senior acupuncturists. All of the investigators were qualified to perform this study after they participated in special training classes about this trial and were tested to well understand the research. For instance, they were trained to use the randomization number table, to fill in the case report form, to identify the correct acupoints, to manipulate the needles, and so on. In addition, to ensure the quality of the study, the clinical monitors will check the process of the trial and document the details of the processes once a week. Moreover, monitors nominated by the principal investigator will check the accuracy and validity of the original data from the clinical center. Regular meetings will be held to consider the recruitment rate, adverse events, protocol violation, difficulties and problems emerging during the study, and so forth.

### Ethics approval and registration

2.16

This clinical trial will be carried out in accordance with the Declaration of Helsinki, as well as be reviewed and approved by the Medical Ethics Committee Board of Affiliated Bao’an TCM Hospital of Guangzhou University of Chinese Medicine (Grant No: 20160923). All of the participants will be requested to sign the written informed consent form before randomization. The present study is financially supported by the National Natural Science Foundation of China (Grant No: 81574064; 81473755), the Shenzhen Science and Technology Planning Project (grant No: JCYJ20170306152650625), and the Shenzhen Bao’an Traditional Chinese Medicine Hospital Research Program (Program No. BAZYY20200609). The clinical trial was registered in the Chinese Clinical Trials Registry in May 2017.

## Discussion

3

This study is a randomized, controlled, assessor-statistician-blinded, positive medicine clinical trial, funded by the National Natural Science Foundation of China. The purpose of this project is to verify the efficacy and safety of acupoint thread embedding on PMOP. The goal is hoped can be achieved by evaluating BMD measurement, fMRI, clinical integral scale, etc. This study is based on syndrome differentiation of viscera (kidney syndrome differentiation) to determine the acupoints used in thread embedding therapy. The researchers searched papers for nearly 10 years and found that the treatment of osteoporosis based on viscera syndrome differentiation (kidney syndrome differentiation) is effective. It has been investigated that many cases of osteoporosis patients in Nanjing responded to the treatment of “ tonifying kidney and benefiting marrow” method. In the treatment of osteoporosis, the method has achieved good evaluation.^[13]^ In TCM theory, “kidney controls bones and marrow moistens bones,” which means that the kidney essence can improve the growth and development of human, and bone formation. Broadly speaking, the kidney essence consists of marrow, spinal cord, and brain. And the brain is the “marrow sea”; it plays a leading role in the growth and development of bone. The kidney affects the growth and development of bone by its close connection with the brain. Combining with the theory of “brain-bone mass regulation” in modern medicine,^[14]^ the researchers believe that the method of “tonifying kidney and benefiting marrow” affects kidney and brain, then influences bone metabolism, and is a symptomatic treatment for osteoporosis.

Furthermore, the previous study found that acupoint stimulation has certain effect on perimenopausal syndrome.^[9]^ Therefore, the study is designed by thread embedding therapy at acupoints after syndrome differentiation, in order to provide evidence for the clinical efficacy and the effect of the brain-bone mass regulation mechanism in the nervous center.

In addition to using SF-MPQ, OQOLS, ECOS-16, and osteoporosis symptom scores to evaluate clinical efficacy, the study also chose BMD measurement and MRI scan to provide clear, effective, and visible evidence to verify the efficacy and safety of acupoint thread embedding on PMOP.

The study found several evidences about acupuncture (acupoint stimulation) treatment of PMOP^[9,15]^ and changes in bone mass caused by changes in brain endocrine hormones. Studies have shown that when the original bone resorption and bone formation balance is broken, after that, bone resorption increases, bone formation decreases, and osteoporosis is induced or aggravated.^[16,17]^ Bone physiology is coordinated by brain control and is associated with the transmission of leptin signaling.^[18]^ Hypothalamus release neurotransmitters via neuropeptides and monoamines, which regulate the secretion of gonadotropin-releasing hormone, growth hormone-releasing hormone, and thyrotropin-releasing hormone, interfering with bone growth and metabolism.^[19]^ Decreased expression of protein kinase C, bone morphogenetic protein, and its signal transduction molecule in osteoporosis model rats can significantly increase BMD.^[20,21]^ Acupoint embedding may regulate the neuroendocrine function by regulating the secretion of gonadotropin-releasing hormone (GnRH), growth hormone-releasing hormone (GHRH), and thyroid-stimulating hormone-releasing hormone (TRH) in the arcuate nucleus of the hypothalamus through monoamine neurotransmitters, then adjust the bone mass.^[19]^ Acupuncture (acupoint stimulation) can improve the symptoms of PMOP to some extent, and found that the brain's hormone levels have changed. Therefore, the researchers hypothesized that acupoint thread embedding therapy can improve the symptoms of PMOP and designed the study.

Nevertheless, there are also limitations in this study. Concerning the unfeasible blinding to participants, one limitation is the possibility of a high risk of bias regarding blinding by unconcealed allocation. Therefore, we strictly conduct randomization and separate the acupuncturist, assessor, and statistician. Meanwhile, patients divided into the acupuncture intervention group may have more opportunities to make contact with their acupuncturists and establish a good doctor--patient relationship rather than those of the medicine control group, which is likely to improve the therapeutic effect. Hence, we will maintain close contact with patients in the control group by telephone, Internet, and so on to minimize this potential bias. At the same time, BMD is one of the important indicators of this study, but the change of BMD is not visible in the short term, which does not match the 3-month cycle of this study. However, as the main diagnostic index of PMOP, BMD cannot be ignored, so it remains in the experiment. To this end, researchers seek breakthroughs in neuroimaging, with a view to finding early imaging markers through fMRI before and after treatment, and judging the efficacy with other indicators such as symptom scale.

In conclusion, combining fMRI, BMD, and subjective symptom scale, the relevant outcomes are predicted to verify the efficacy and safety of acupoint thread embedding therapy. We believe that the results will exert a positive effect on acupoint thread embedding treatment for PMOP.

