### Objectives

2.1

This study aims to investigate the efficacy and safety of acupoint thread embedding treatment on PMOP and explore its neural mechanism.

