### Trial design and study setting

2.2

This study is a parallel designed, exploratory randomized, controlled, assessor-statistician-blinded, positive medicine clinical trial. Seventy participants with PMOP will be randomly assigned to the treatment group (taking acupoint thread embedding treatment, n = 35) and a control group (taking Climen treatment, n = 35) in a 1 : 1 ratio. The trial design and study flowchart are shown in Fig. 1.

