#### Adverse events

2.9.4

During the research, some adverse reactions may occur. Researchers will monitor every patient with adverse reaction.

The following adverse reactions may happen after the acupoint thread embedding:

(1)Local reaction: mostly some sterile inflammation with inflamed hot pain within 5 days. Some cases may be more severe, like a small amount of milky-white exudation at the embedding spot caused by fat liquefaction because of thread stimulation. Circumstances above should not require any special treatment.(2)General reaction: some patients may experience temperature rising after the treatment 4 to 24 hours, which mostly around 38°C. It will fade away in 2 to 4 days by itself. Usually, hemogram of each patient may rise in different levels, and it will return to normal in 3 to 5 days.

If adverse reactions occur, the following treatment will be used.

(1)Pain at implantation acupoint: Apply hot compress.(2)Local swelling, progressive pain, and fever 3 to 4 days after the implantation: Lack of strict asepsis and inappropriate protection of the wound could cause secondary infection, which mostly occurs some inflammatory symptoms. Apply hot compress and anti-infective treatment would help.(3)Nerve injury: It is usually caused by incorrect operation or excessive stimulation or carelessness, and can be avoided with the careful operation.(4)Hemorrhage: It is usually caused by the puncture on the vessels or excessive stimulation, in which case pressure dressing on the puncture point would stop the bleeding.(5)Thread allergy: local itching or swelling or fever can be remitted by antianaphylaxis treatment.

Climen, which includes estradiol and cyproterone acetate, is one of the estrogen and progestogen/anti-androgen (HRT). It is used in HRT for women with an intact uterus, used to substitute for a lack of estrogen production by the ovaries during menopause. It helps prevent postmenopausal bone loss (osteoporosis) and reduce risk of fracture. The most commonly reported side effects when taking Climen include breast tenderness, breast pain, abdominal pain, nausea, edema, headache, depression, changes in body weight, and changes in libido.

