### Statistical analysis

2.14

Image data processing includes using methods such as independent component analysis (ICA) and function binding, applying professional software such as MRIcro for windows, Xjview 8.1, SPM 12, and Matlab 5.1.

Statistical analysis technique is used to apply a statistical test to the difference of prior-treatment and posttreatment, and to examine the curative effect difference within groups and among groups of all curative effect indexes. We will adopt the 2-sided test for all statistical tests. It is considered that the tested differences are statistically significant if *P* value is less than or equal to .05. If *P* value is greater than or equal to .05, the tested differences are not statistically significant. Details are as following.

Measurement data includes the *t* test will be adopted to run comparison among groups. When it does not comply with the normal distribution, we will choose Wilcoxon rank-sum test. Similarly, we will run paired *t* test toward the difference of prior-treatment and post-treatment, and it will be changed into Wilcoxon rank-sum test, while it does not comply with the normal distribution.

Enumeration data: We will use the Chi-square test, calibration Chi-square test, and Fisher exact method to run comparison among groups.

Ranked data: Wilcoxon rank-sum test will be applied to run comparison among groups and signed rank-sum test to run comparison within groups.

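### The Discussion promises to verify efficacy, but the exploratory tests against an active drug cannot do so from a non-significant difference or a within-arm gain

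*Protocol article*

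**What the plan says.** Aim. The Discussion (section 3) says: "The purpose of this project is to verify the efficacy and safety of acupoint thread embedding on PMOP". Its closing paragraph adds that "the relevant outcomes are predicted to verify the efficacy and safety of acupoint thread embedding therapy". The Methods are more modest. Section 2.1 has "This study aims to investigate the efficacy and safety of acupoint thread embedding treatment on PMOP and explore its neural mechanism", and section 2.2 has "This study is a parallel designed, exploratory randomized, controlled, assessor-statistician-blinded, positive medicine clinical trial"; the Abstract also uses the exploratory label.

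Design. Section 2.2 describes two arms of 35, embedding and "a control group (taking Climen treatment, n = 35) in a 1 : 1 ratio". No sham, placebo or untreated arm is described. Section 2.8 says that participants and practitioners cannot be blinded, while the assessor, data collector and statistician are. Section 2.10 makes the SF-MPQ and the Osteoporosis Symptom Score the primary outcomes.

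Analysis. Section 2.14 sets out "to examine the curative effect difference within groups and among groups of all curative effect indexes", using two-sided tests at .05. The between-arm comparison is a t test and the pre/post comparison a paired t test, each with a rank-based alternative. The only decision rule is whether a difference is significant. No non-inferiority or equivalence margin is given.

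Comparator. Section 2.9.4 describes Climen as hormone replacement that makes up for lost oestrogen, and says: "It helps prevent postmenopausal bone loss (osteoporosis) and reduce risk of fracture". It states no effect of Climen on either primary scale.

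**The concern.** Section 3 sets a confirmatory aim for a trial that section 2.2 labels exploratory, and section 2.14 does not say which results would meet that aim. Three kinds of result are possible, and they differ in what they can support.

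- **Embedding significantly better than Climen.** This is evidence of benefit, subject to the fact that the scales are completed by patients who know their treatment.
- **No significant difference.** Without a margin this does not show comparability. Even real similarity would not show that embedding works, because the article does not state that Climen works on these scales.
- **Improvement within the embedding arm.** This mixes any specific effect with natural course, regression to the mean, expectation and practitioner contact. Section 3 itself accepts that contact is likely to improve the apparent effect.

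Section 2.14 lists the within-arm tests among the analyses of curative effect, on the same footing as the between-arm tests. Nothing in the text therefore bars the second or third kind of result from being offered as verification. What is at stake is which conclusion the trial may draw.

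**Working it through.** The article gives 70 participants (35 per arm) with no effect size, SD, power or margin, so there is no sample-size derivation to reproduce. The check asks what the planned tests can show at that size.

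**Inputs from the document:** n = 35 per arm (section 2.2); two-sided alpha .05, t test between arms and paired t test within arms (section 2.14).

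**Assumptions, not from the document:** no dropout; true effects in SD units, shown as a range; normal outcomes with equal SD.

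**1. Precision of the between-arm difference**

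Half-width of the 95% CI = t(0.975, 68) × √(2/35) = 1.995 × 0.2390 = 0.477 SD.

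Even with an observed difference of exactly zero, the interval runs from about −0.48 to +0.48 SD.

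**2. Chance of missing a true deficit**

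Noncentrality = d / √(2/35), with 68 degrees of freedom.

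| True deficit of embedding (assumed) | Noncentrality | Power | Non-significant |
|---|---|---|---|
| 0.3 SD | 1.255 | 23.6% | 76.4% |
| 0.5 SD | 2.092 | 54.1% | 45.9% |

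Absence of significance is thus common even when embedding is truly worse than Climen.

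**3. Chance of a significant within-arm test with no specific effect**

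Suppose embedding has no specific effect, but the mean change drifts by d, in units of the SD of the change. Noncentrality = d × √35, with 34 degrees of freedom and critical value 2.032.

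| Drift (assumed) | Noncentrality | Paired test significant |
|---|---|---|
| 0.3 | 1.775 | 40.7% |
| 0.5 | 2.958 | 82.0% |

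The unit matters. If drift is measured in SDs of the score itself, these figures hold at a pre/post correlation of 0.5, because the SD of the change is then √(2 × (1 − 0.5)) = 1. At a correlation of 0.7 they rise to about 61% and 96%.

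**4. Whether similarity to Climen could stand in for efficacy**

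This needs a stated effect of Climen on the primary scales. Section 2.9.4 credits it with oestrogen replacement, prevention of bone loss and lower fracture risk. The Introduction says in general terms that modern therapies, with hormone replacement named among them, are efficacious for PMOP. Neither statement concerns SF-MPQ or symptom scores over 12 weeks, so that step is unsupported.

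**The case against.** The strongest reply has four parts.

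*The operative sections are modest.* The Abstract and sections 2.1 and 2.2 say investigate, explore and exploratory; *verify* is found only in the Discussion, which sets no decision rule. This is fair, and it limits the point to an inconsistency that wording can cure. It does not remove it, because section 3 states the project's purpose and repeats the claim in its conclusion.

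*A two-sided test against an active drug is a legitimate superiority test.* This stands in full. A significant advantage for embedding would be evidence of efficacy, so it would be wrong to say that the design can never support an efficacy claim.

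*The article never says that a null result will be read as equivalence, or a paired P value as proof.* This also stands. A reader might infer that the authors expect both arms to improve without a difference and would report that as verified efficacy. The document neither predicts that result nor says how it would be read. What can be said is that section 2.14 counts the within-arm test as a curative-effect analysis and that nothing excludes such a reading. Interpretation rules can be left to an SAP, but the tests and the decision rule are already fixed here.

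*Bias is acknowledged.* Section 3 names the lack of participant blinding and the unequal contact as limitations; section 2.8 blinds the assessor, and section 2.15 gives controls weekly face-to-face and daily remote contact. These measures help the between-arm comparison. They do nothing for a pre/post test within one arm.

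Two further overstatements should be avoided. A reader might infer that bone protection is the only benefit credited to Climen; given the Introduction, the supportable statement is that no benefit on the primary scales is stated. A reader might also double the half-width and say that embedding could be about 0.95 SD worse (2 × 0.477). That applies only when embedding is already observed to be about 0.48 SD worse, which nobody would call similar.

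**Conclusion.** The point holds in a conditional form. The aim of verifying efficacy in section 3 conflicts with the exploratory label in section 2.2, and the tests in section 2.14 could support it only through a significant between-arm advantage for embedding, qualified by unblinded patient reporting. Under the assumptions shown above, neither of the other results can support it: a non-significant difference leaves too wide an interval and misses moderate deficits too often, and a within-arm gain is readily significant with no specific effect. The sizes are illustrative, since the article gives no SD or expected effect, and dropout would widen the interval. The argument about inference does not depend on the particular values chosen. This should be corrected before results are reported.

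**What to change.** In section 2.14:

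- state that efficacy statements rest on the between-arm difference in the primary outcomes, reported with its 95% CI;
- state that a non-significant difference is inconclusive and is not evidence of comparability;
- make within-arm changes descriptive, with no P value used as proof of effect.

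In section 3, replace *verify*, in both the opening statement of purpose and the conclusion, with wording such as *explore* or *estimate the difference from Climen*, so that it agrees with sections 2.1 and 2.2.

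This needs no extra arm, patients or margin. A margin would be required only if the trial wished to claim non-inferiority, which it does not now do. The cost is a less favourable claim if the between-arm result is not significant.

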## Abstract

**Introduction::**

Postmenopausal osteoporosis (PMOP), which is a common and frequently occurring age-related metabolic bone disease in perimenopausal women, severely affects patients living quality. Modern medicine therapies for PMOP have several problems such as side reactions, low compliance, and high costs. Thus, nonpharmacological modality is urgently needed. Although acupoint thread embedding treatment is widely used in clinical practice, there is no persuasive evidence of its effect on increasing bone mass for PMOP. This experiment aims to investigate the efficacy and safety of acupoint thread embedding on PMOP and elucidate the correlations among brain neural activation, bone mineral density (BMD), and clinical outcomes with magnetic resonance evidence, thus to explore its neural mechanism.

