#### Study schedule

2.9.1

The study schedule is presented in Table 1. At the screening visit, participants will sign the informed consent form. In a baseline questionnaire, the following information will be obtained: age, occupation (physical/nonphysical), education level, last menstrual period, previous use of acupuncture, and expectation to acupoint thread embedding treatment. Moreover, Short-Form of McGill Pain Questionnaire (SF-MPQ), Osteoporosis Symptom Score, Osteoporosis Quality of Life Scale (OQOLS), 16-item Assessment of Health-Related Quality of Life in Osteoporosis (ECOS-16) must be completed at the baseline (week 0). Thereafter, study subjects will be randomized. There is a 3-month study period and a 1-month follow-up period for each group. In the study period, SF-MPQ, OQOLS, ECOS-16, and Osteoporosis Symptom Score will be evaluated every 4 weeks. fMRI and bone density test will be tested 2 times: in week 0 and week 12.

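### Week-12 BMD is still named as efficacy evidence although the protocol says BMD change is not visible in 3 months, and no later bone scan exists against which an fMRI marker could be called early

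*Protocol article*

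**What the plan says.** The Abstract identifies the gap as bone mass: "there is no persuasive evidence of its effect on increasing bone mass for PMOP". It then sets out to "elucidate the correlations among brain neural activation, bone mineral density (BMD), and clinical outcomes with magnetic resonance evidence".

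Section 2.9.1 fixes the timing: "fMRI and bone density test will be tested 2 times: in week 0 and week 12". On duration it says: "There is a 3-month study period and a 1-month follow-up period for each group". No bone scan is scheduled after week 12.

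BMD is not among the primary outcomes (section 2.10) or the secondary outcomes (section 2.11). Section 2.12 treats it separately, as a gauge of how severe the osteoporosis is. Section 2.14 applies two-sided tests at 0.05, before against after and between groups, to every curative-effect index, without listing those indexes.

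The Discussion first lists BMD among the means of reaching the efficacy goal and presents BMD and MRI as visible proof of efficacy. Its limitations paragraph then says that "the change of BMD is not visible in the short term, which does not match the 3-month cycle of this study". It keeps BMD because it is the main diagnostic index, and turns to neuroimaging "with a view to finding early imaging markers through fMRI before and after treatment", with efficacy judged by other indicators such as the symptom scale. The closing paragraph returns to BMD: "combining fMRI, BMD, and subjective symptom scale, the relevant outcomes are predicted to verify the efficacy and safety of acupoint thread embedding therapy".

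**The concern.** BMD cannot serve as visible proof of efficacy if its change is, by the protocol's own account, not visible over the study period. The concession is made, but BMD's stated role does not change after it.

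The proposed way round the problem has a gap of its own. A marker of bone response is early only relative to a bone response measured later. Here the two measures share both time points and nothing follows.

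Three misreadings are left open:

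- A non-significant BMD difference between embedding and Climen could be taken as equal effect on bone, when it may reflect only the short interval.
- A within-arm rise could be taken as benefit, although a before-after test has no randomised comparison behind it.
- An association between fMRI change and BMD change over the same 12 weeks could be presented as an early marker.

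**Working it through.** **1. Statements on BMD side by side**

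| Place | Role given to BMD |
|---|---|
| Abstract, Introduction | Bone mass is the evidence gap; BMD is one of three quantities to be correlated |
| 2.9.1 | Measured at weeks 0 and 12 only, the same times as fMRI |
| 2.10, 2.11 | Neither primary nor secondary |
| 2.12 | Severity of disease |
| 3, first part | Evidence to verify efficacy |
| 3, limitations | Change not visible within 3 months |
| 3, closing paragraph | Again combined with fMRI and scales to verify efficacy |

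The severity role in 2.12 is compatible with the limitation. The efficacy role in the first and closing parts of the Discussion is not.

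**2. Timing of the marker.** The last fMRI is at week 12 and the last BMD is at week 12, so there is no interval between marker and response. Any association between their changes is concurrent.

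**3. Illustration of size.** The article gives no power, effect size or SD for BMD, so there is no figure to reproduce. From the documents: 35 per arm, 70 in total, two-sided 0.05. *Assumed, not in the documents:* DXA precision error (CV) 1–2%, SD of true 12-week change 0.5–1.0%, true correlation between fMRI change and BMD change 0.5, no dropout, fMRI change measured without error.

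*Between-arm difference.* The difference detectable with 80% power is (1.960 + 0.842) × √(2/35) = 0.67 SD. Scan error alone gives a change-score SD of √2 × CV. True variation between women would only widen it.

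| CV | SD of change, scan error only | Detectable difference (0.67 SD) | Power for a true 0.5% difference | 95% CI half-width, 1.960 × SD × √(2/35) |
|---|---|---|---|---|
| 1.0% | 1.41% | 0.95% | 32% | 0.66% |
| 1.5% | 2.12% | 1.42% | 17% | 0.99% |
| 2.0% | 2.83% | 1.89% | 11% | 1.33% |

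Under these assumptions an observed difference of zero would be compatible with at least ±0.66% to ±1.33%.

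*Correlation of changes.* Reliability of the BMD change = SD_true² / (SD_true² + 2 × CV²). Observed r = 0.5 × √reliability. Power is by Fisher z with standard error 1/√(n − 3).

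| CV | SD of true change | Reliability | Observed r | Power, n = 35 | Power, n = 70 |
|---|---|---|---|---|---|
| 1% | 1.0% | 1/(1 + 2) = 0.33 | 0.29 | 39% | 68% |
| 1% | 0.5% | 0.25/(0.25 + 2) = 0.11 | 0.17 | 16% | 28% |
| 2% | 1.0% | 1/(1 + 8) = 0.11 | 0.17 | 16% | 28% |
| 2% | 0.5% | 0.25/(0.25 + 8) = 0.03 | 0.09 | 8% | 11% |

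With no error in either measure, r = 0.5 would be detected with power of 87% (n = 35) or 99% (n = 70).

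**The case against.** The authors disclose the mismatch, give a reason for keeping BMD, and say efficacy will be judged by other indicators. The trial is labelled exploratory, and its hypothesis in the Discussion concerns symptoms. Section 2.12 already gives BMD a severity role. All of this stands. It limits the point to BMD and explains why the remedy is mostly wording. It does not remove the contradiction, because the closing paragraph restores BMD as efficacy evidence after the concession.

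The early-marker criticism involves some inference: the article does not say what the marker is early for. Bone response is the natural reading, because the sentence is offered as the answer to slow BMD change.

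A reader might go further in four ways that the documents do not support.

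- *That the correlation aim is unanswerable.* The Abstract does not specify change scores, and section 2.14 describes no correlation analysis. Cross-sectional correlations at baseline fit the stated aim and do not need BMD to change.
- *That selecting women on a low T-score will make the second scan drift upward.* Section 2.4 does not date the qualifying scan, and Table 1 is not reproduced in the text at hand. Any such drift would be expected equally in both randomised arms and would cancel between them.
- *That noise will produce a false efficacy finding between arms.* A single between-arm test keeps its 5% error. The exposure lies in within-arm tests, exploratory correlations and the reading of a null result.
- *That the trial already claims equal bone effect.* It makes no such claim; the point is to rule it out in advance.

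**Conclusion.** The point holds as an internal inconsistency. The protocol says BMD change is not visible within its 3 months, yet names BMD as evidence that will verify efficacy. With fMRI and BMD both ending at week 12, no fMRI change can be shown to be an early marker of later bone response. These conclusions rest on the text alone.

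The size is illustrative, because every BMD input is assumed. Over the stated ranges, a true correlation of 0.5 would appear as 0.09–0.29, with power of 8–39% within an arm or 11–68% with both arms pooled. The smallest between-arm difference detectable with 80% power would be at least 0.95–1.89%. The spread shows how little the article fixes. The fall from 87% or 99% overstates the loss due to DXA to the extent that fMRI change also carries error.

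The SF-MPQ and Osteoporosis Symptom Score comparisons are untouched. The correction should be made because it changes what the trial may conclude about bone, but it does not threaten the primary analysis.

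**What to change.** Reconcile the Abstract, section 2.12 and the Discussion as follows.

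1. Define BMD as a baseline severity measure: correlate baseline BMD with baseline fMRI and baseline scales, and use it as a covariate.
2. Report week-12 BMD descriptively, with between-arm estimates and confidence intervals. Draw no efficacy conclusion from within-arm change, and say in section 2.14 that BMD is not one of the curative-effect indexes.
3. State that a null 12-week BMD difference from Climen is not evidence of equal bone effect.
4. Base the neural-mechanism aim on fMRI change against change in SF-MPQ and Osteoporosis Symptom Score.
5. Replace the early-marker wording with *concurrent associations*, and remove BMD from the sentences that say which measures will verify efficacy.

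The cost is wording and analysis specification, with no new visit or scan. The article reports the trial as still recruiting, so the change can precede analysis. What is given up is a bone-mass efficacy claim that the study's duration cannot support.
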